# Acupuncture for acute stroke: study protocol for a multicenter, randomized, controlled trial

**DOI:** 10.1186/1745-6215-15-214

**Published:** 2014-06-08

**Keywords:** Acupuncture, Stroke, Multicenter RCT

## Abstract

**Background:**

Acupuncture has been widely used as a treatment for stroke in China for more than 3,000 years. However, previous research has not yet shown that acupuncture is effective as a stroke treatment. We report a protocol for a multicenter, randomized, controlled, and outcome assessor-blind trial to evaluate the efficacy and safety of acupuncture on acute ischemic stroke.

**Methods/Design:**

In a prospective trial involving three hospitals in the Zhejiang Province (China) 250 patients with a recent (less than 1 week previous) episode of ischemic stroke will be included. Patients will be randomized into two groups: an acupuncture group given scalp acupuncture and electroacupuncture, and a control group given no acupuncture. Eighteen treatment sessions will be performed over a three-week period. The primary outcome will be measured by changes in the National Institutes of Health Stroke Scale score at the one, three, and four-week follow-up. Secondary outcome measures will be: 1) the Fugl-Meyer assessment scale for motor function; 2) the mini-mental state examination and Montreal cognitive assessment for cognitive function; 3) the video-fluoroscopic swallowing study for swallowing ability; and 4) the incidence of adverse events.

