#### Primary outcome measurement

The primary outcome measurement in the study is the change in NIHSS scores for neurological deficit evaluation. NIHSS is a standardized stroke severity scale used to describe neurological deficits in stroke patients and it strongly predicts the likelihood of a patient’s recovery after stroke. The NIHSS comprises tests of 11 items including the level of consciousness, best gaze, visual field, facial palsy, motor arm, motor leg, limb ataxia, sensory ability, best language, dysphagia, and neglect. Total scores range from 0 to 42, with scores above 25 indicating very severe neurological impairment, scores of 5 to 24 suggesting moderately severe to severe impairment, and scores below 5 indicating mild impairment
[19]. Assessments will be conducted at baseline and at one, three and four-weeks follow-up.

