### Sample size calculation

The primary efficacy parameter is the change in NIHSS scores from baseline to the end of treatment after three weeks. According to our preliminary test and previous study
[26], the decrease in NIHSS score was conservatively estimated to be 5 in the acupuncture group and 3 in the control group, with a standard deviation of 5.0. A two-sided 5% significance level and 80% power were considered, and the following equation was used:

(1)n=2za2+zβ2σ2Δ2

Approximately 100 participants in each group were calculated to be required. Estimating a 20% dropout rate, each group will require 125 initial participants.

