### Statistical analysis

All data will be analyzed by a blinded statistician using the SPSS(Statistical Product and Service Solutions) statistical package program (version 17.0, SPSS Inc., Chicago, Illinois, United States) at a separate location from the clinical research institute of Zhejiang Provincial Hospital of Chinese medicine. Baseline data will be collected and compared first. All patients randomized to each group are included in the analysis and the data analysis will be conducted using two-sided significance tests at the 5% significance level. The analysis of swallowing disorder and cognitive impairment will be made on the defined population of corresponding dysfunction in the baseline assessment. Different statistics are presented differently; for example, continuous variables will be expressed as mean ± SD, *t*-test will be used for comparisons of two independent samples, and non-parametric tests will be used for variables that do not follow a normal distribution. A *P* value of less than 0.05 (α value of 0.05) is considered to indicate statistical significance. A safety analysis will be performed by analyzing the frequency of adverse events suspected as related to the treatment. The data for adverse events are collected through the symptoms reported by the patients, and observations by a researcher at every visit.

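### The abstract makes the NIHSS change at three visits the primary outcome, the sample size section names and powers only the three-week change, and nothing says which definition governs

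*Protocol article*

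**What the plan says.** Four places in the protocol article bear on this point.

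- **Abstract, Methods/Design.** The primary outcome is measured by "changes in the National Institutes of Health Stroke Scale score at the one, three, and four-week follow-up". Change at three visits is primary.
- **Primary outcome measurement.** "The primary outcome measurement in the study is the change in NIHSS scores for neurological deficit evaluation". The section ends with a schedule: "Assessments will be conducted at baseline and at one, three and four-weeks follow-up". It does not say that the change at each visit is a primary outcome, and it does not pick one visit.
- **Sample size calculation.** "The primary efficacy parameter is the change in NIHSS scores from baseline to the end of treatment after three weeks". The calculation is for that single comparison: "A two-sided 5% significance level and 80% power were considered".
- **Statistical analysis.** "the data analysis will be conducted using two-sided significance tests at the 5% significance level", and a P "value of less than 0.05 (α value of 0.05) is considered to indicate statistical significance". The t-test "will be used for comparisons of two independent samples", with non-parametric tests where normality fails. The section does not return to which NIHSS visit is primary.

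The timing of the last visit also varies. The outcome assessment section places a four-week follow-up after the end of the three-week treatment course, which is about week 7. The abstract and the primary outcome section give one, three and four weeks in a row, which can be read as week 4.

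**The concern.** The time point of the primary endpoint is a protocol-level decision, and here it is stated in two ways that cannot both hold. A reader of the abstract expects three primary comparisons. A reader of the sample size section expects one. Because the document does not rank the two statements, either could be cited after the results are known.

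The stakes are the error rate and the credibility of the efficacy conclusion. The 5% level and 80% power were set for one test at one visit. If a favourable result at any of three visits could be presented as the primary result, the 5% no longer describes the risk of a false claim. The uncertain date of the last visit makes this slightly worse, since one of the three candidate visits is not clearly fixed.

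**Working it through.** **Inputs from the sample size section.** Decrease in NIHSS of 5 points against 3, so Δ = 2; SD σ = 5; two-sided α = 0.05; power 80%; dropout 20%.

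**Input not in the document.** The correlation between visits of the treatment comparisons. It is assumed equal for all pairs of visits and varied from 0 to 0.9.

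**Step 1: reproduce the stated sample size.**
n per group = 2(1.96 + 0.8416)² × 5² / 2² = 2 × 7.849 × 6.25 = 98.1, rounded up to 99, against the stated figure of about 100. Dropout: 100 / (1 − 0.20) = 125 per group, 250 in total. Both figures reproduce for one two-sided 5% test at one visit, so they contain no allowance for three primary tests.

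**Step 2: error rate and power under the sample size definition.** One test, so the error rate is 5%. With 100 per group the standard error is 5 × √(2/100) = 0.707 and the standardised effect is 2 / 0.707 = 2.83. Power is 80.4% from the t distribution (80.7% by the normal approximation).

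**Step 3: error rate if the abstract governed and any visit counted.** Under independence this is 1 − 0.95³ = 14.3%. For correlated visits, three equally correlated two-sided z-tests at the 5% level were simulated:

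| Assumed correlation | Chance of at least one false positive |
|---|---|
| 0 | 14.3% |
| 0.5 | 12.5% |
| 0.7 | 10.9-11.0% |
| 0.8 | 9.8% |
| 0.9 | 8.3-8.4% |

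Ranges show variation between simulation runs. The figures count a false positive in either direction. Counting only those that favour acupuncture roughly halves them (6.2% at 0.5 and 4.2% at 0.9), and the comparator is then 2.5%. The relative inflation is about the same.

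**Step 4: would a Bonferroni correction lose the power?** At α = 0.05/3 = 0.0167, power for one named visit with 100 per group is about 66%. A Bonferroni rule, however, goes with a claim of success on at least one visit. Assuming the same 2-point effect at each visit, the simulated power of that claim is:

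| Assumed correlation | Power for at least one visit |
|---|---|
| 0.5 | 88% |
| 0.7 | 83% |
| 0.8 | 80% |
| 0.9 | 76% |

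So this route does not show that the planned 80% is lost. It falls below 80% only above a correlation of about 0.8.

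**The case against.** The best defence is that the body of the article already names one endpoint. The sample size section fixes scale, baseline and time point, and the stated sample size reproduces for it. The primary outcome section is compatible with that reading, because it gives only a visit schedule. On this view the conflict is one condensed abstract sentence against more specific body text, and under the body text the error rate is 5%. The analysis section sets a general 5% level and does not call each visit a primary test. Multiplicity rules and the handling of repeated visits are commonly left to a statistical analysis plan, which is not shown.

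Much of this stands. The primary outcome section should be cited only as unspecific. The absence of an adjustment or a repeated-measures model is not in itself a fault of this article. The inflation in the table arises only if the abstract's definition is followed. The 14.3% is a ceiling, since changes that share a baseline in the same patients are unlikely to be independent.

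The contradiction itself survives. Nothing tells the reader that the sample size section overrides the abstract, and an analysis plan that settled the matter would have to depart from one of the two.

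Two stronger readings are tempting and are not supported. A reader might infer that the trial will run three unadjusted primary tests and so has an inflated error rate. The documents do not say so, and one of their two definitions excludes it. A reader might also infer that protecting three visits by Bonferroni would cut power to 66%. That is the power for one named visit, not for a claim on at least one. Nor does any section propose that all three visits must succeed.

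**Conclusion.** The point holds as an internal contradiction about the deciding endpoint. The abstract makes the NIHSS change at three visits primary, the sample size section makes the three-week change primary, and the primary outcome section does not settle it.

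Its size depends on which definition is used. Under the sample size section there is no inflation, and power is about 80% with 100 evaluable per group. Under the abstract, with success allowed on any visit at 5% each, the false-positive rate of the primary claim would be about 8-13% instead of 5%. That range rests on assumed correlations of 0.9 to 0.5, because the document gives none. Every value examined, from independence to 0.9, exceeds 5%, so the direction does not depend on the choice. No loss of the planned power is established.

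**What to change.** - In the abstract and in the primary outcome section, name the change in NIHSS from baseline to the end of treatment at three weeks as the single primary endpoint, as the sample size section already does.
- List the one-week and post-treatment NIHSS comparisons as secondary.
- State that the efficacy conclusion rests on the three-week test alone.
- Reconcile the timing of the last visit, so that the abstract, the outcome assessment section and the primary outcome section give the same date counted from the same origin.

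The changes should be made and dated before database lock. They are to wording only: the sample size stays at 125 per group and no new data are needed. The only cost is giving up the option to claim success on another visit. Keeping all three visits as primary would instead require a stated rule across visits and a sample size justified for that rule.

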**Discussion:**

This trial is expected to clarify whether or not acupuncture is effective for acute stroke. It will also show if acupuncture can improve motor, cognitive, or swallowing function.

**Trial registration:**

Chinese Clinical Trial Registry
ChiCTR-TRC-12001971.

## Background

Stroke is a major cause of death and disability worldwide
[1-3]. It is also the leading cause of death and long-term disability in China
[4,5], where a rising incidence of stroke has created a serious public health problem
[6,7]. Despite a considerable amount of research on treatment for stroke there is still no single intervention that clearly and definitely contributes to stroke recovery. However, there is no doubt that the treatment of stroke should be combined with multiple disciplines such as neurology, rehabilitation medicine, and traditional medicine. Acupuncture has been used in traditional Chinese medicine for more than 3,000 years as a treatment for many diseases and is especially well accepted in China for post-stroke rehabilitation
[8]. Because stroke is one of the most common uses of acupuncture therapy, many Chinese acupuncture departments have set up special wards to treat stroke patients to maximize the promotion of recovery. It has been shown that acupuncture can cause multiple biological responses including circulatory and biochemical effects
[9,10]. As a therapeutic intervention acupuncture is used to improve motor, sensation, speech, swallowing, cognitive, and other neurological functions in patients with stroke
[11,12]. Scalp acupuncture seems to improve the neurological deficit score and clinical effective rate when compared with Western conventional medicines alone
[13], and it produces positive but limited effectiveness as an adjunct treatment to conventional care
[14]. Electroacupuncture appears to be beneficial for the motor function recovery of patients with acute ischemic stroke and is generally safe
[15]. However, Cochrane reviews have shown that while acupuncture appears to be safe, there is no clear evidence of benefit
[16]. Therefore, there is insufficient data on the routine usage of acupuncture in acute stroke. More rigorously designed, large, multicenter, randomized trials are needed to further assess the effectiveness of acupuncture on stroke rehabilitation.

## Methods/Design

### Study design

The study is a prospective, multicenter, outcome assessor-blinded, randomized controlled clinical trial carried out in three inpatient stroke rehabilitation units. After the inclusion and consent of the Institutional Review Board, participants will be randomized to either the control (no acupuncture) or the acupuncture group. The control group will receive conventional stroke rehabilitation care (including physical and occupational therapy, swallowing training for dysphagia, and/or cognitive training for cognitive impairment; six days per week) during the inpatient stay. The acupuncture group will receive conventional stroke rehabilitation care and 30 additional minutes of acupuncture therapy six days per week for three weeks (18 total acupuncture sessions) during the inpatient stay. The trial design is summarized in Figure 
1.

**Figure 1 F1:**
[figure not shown]
Flow diagram of study design.

### Participant recruitment

Participants will be recruited in three large hospitals (The Second Hospital of Jiaxing City, Sir Run Run Shaw Hospital, and The First People’s Hospital of Hangzhou) in Zhejiang Province, China. Our study will be propagated by local newspapers, health-related TV programs, the internet, and posters in communities and hospitals. Prospective participants will be asked to talk face-to-face with study coordinators to discuss the study and provide information regarding eligibility criteria. If patients are eligible and interested in participating they will be invited for a series of rehabilitation assessments after diagnosis by neurologists. Two hundred and fifty consecutive patients admitted to the three hospitals because of acute ischemic stroke will be included in the study. When their informed consent has been obtained, patients will be randomized into two groups with different treatments.

### Inclusion criteria

We will choose patients aged between 35 and 80-years-old who are hospitalized with acute ischemic stroke according to the criteria of both Western medicine and traditional Chinese medicine. The stroke onset must be between two to seven days beforehand, with a National Institutes of Health Stroke Scale (NIHSS) score of between 4 and 24. The stroke should be the first incidence or patients can have a history of stroke but without disability (modified Rankin Scale, mRS score ≤1).

### Exclusion criteria

Patients who received thrombolytic therapy or who participated in other clinical trials within last three months are not included. Patients who suffered from serious heart,liver,kidney related diseases, blood coagulation dysfunction, or severe mental disorders will not be included. Women who are pregnant or breast-feeding and patients with a severe cognitive impairment are also excluded.

### Ethical considerations

Each ethics committee of the Third Affiliated Hospital of Zhejiang Chinese Medical University, The Second Hospital of Jiaxing City, and Sir Run Run Shaw Hospital, together with The First People’s Hospital of Hangzhou, all approved the study. The purpose, nature, and potential risks of the experiments were fully explained to the patients and their families. All patients gave their written informed consent before participating in the study.

### Randomization and blinding

Randomization to acupuncture or no acupuncture will be computer-generated by independent research staff using software. The treatment codes are placed in sealed opaque envelopes which will be distributed by research nurses who will be trained before the trial and will not participate in treatment or nursing. Patients in this research will be told that they will receive routine rehabilitation treatment with or without acupuncture. It is impossible to blind the acupuncturists because they must be trained to perform the acupuncture according to the research plan. A special rehabilitation doctor from each center will be assigned to be the assessor who is blinded to the patient treatment group and does not participate in the treatment of subjects. All study personnel including the rehabilitation therapists, outcome assessors, and data analysts will be blinded to group assignments.

### Interventions and comparison

The study is a randomized clinical trial carried out in three inpatient rehabilitation departments of three hospitals. Participants will be randomized to either the control or the acupuncture group. Both groups will receive conventional stroke rehabilitation care, which begins as soon as the diagnosis of stroke is established and life-threatening problems are under control. The basic rehabilitation care includes normal limb posture, passive motion with hemiplegia side, bedside rehabilitation (Bobath technique, overturning movement, bridge movement), and/or neuromuscular electrical stimulation, swallow training for dysphagia, and/or cognitive training for cognitive impairment. The rehabilitation program (including physiotherapy and occupational therapy for two hours per day, six days per week) of each participant will be developed by the rehabilitation team according to the investigator’s brochure. The acupuncture group will receive 30 additional minutes of acupuncture therapy for six days per week for three weeks (18 total sessions) during the inpatient stay.

#### Acupuncture group

The acupuncture protocol is designed by a professor from Zhejiang Chinese Medical University who has more than 20 years of practice experience, and will be performed by three doctors from the acupuncture department who have a master’s degree with more than five years of clinical experience. They will be trained together and use the same techniques. The treatment will be started in both groups after randomization. The acupuncture protocol is split according to the area of treatment.

The parameters for scalp acupuncture are set as follows: two to three needles penetrating through the top midline, the motor region, and the sensory region of the lesion side. The parameters for the affected side of the body are as follows: LI15 (Jian Yu), LI11 (Qu Chi), LI10 (Shou San Li), SJ5 (Wai Guan), LI4 (He Gu) for upper extremities; St34 (Liang Qiu), St36 (Zu San Li), GB34 (Yang Ling Quan), Sp6 (San Yin Jiao), St40 (Feng Long), St41 (Jie Xi), and Liv3 (Tai Chong) for lower limbs. The parameters for acupoint modification are set as follows: For dysphagia, GB20 (Feng Chi), EX-HN14 (Yi Ming), BL10 (Tian Zhu), DU16 (Feng Fu), Gong Xue (1 cun below GB20), RN23 (Lian Quan) will be added. For mild cognitive impairment, DU20 (Bai Hui), DU24 (Shen Ting), GB13 (Ben Shen), EX-HN1 (Si Shen Cong) will be added.

Manual stimulation will be applied to the body acupoints until the patients experience De qi (get Qi). Patients experience De qi as multiple unique sensations at the needle site itself and around the site of needle manipulation, including soreness, aching, numbness, tingling, and even warmth
[17,18]. The parameters for electroacupuncture for LI15 (Jian Yu) and LI11 (Qu Chi), St36 (Zu San Li) and Sp6 (San Yin Jiao) are set as follows: intermittent wave, low-frequency (2 Hz); the intensity is within the scope that patients can tolerate. Huatuo brand needles (size 0.25 mm × 40 mm) were manufactured by Suzhou Medical Appliance in Suzhou, Jiangsu Province China, with GB6805-2 Electro-Acu Stimulators (Huayi Medical Supply & Equipment Co. Ltd, Shanghai, China) used.

#### No acupuncture treatment group

Patients in the control group will receive conventional stroke rehabilitation care, which is the same as the acupuncture group. However, no acupuncture treatments will be given during the study period. They will be assessed at each visit.

### Outcome assessment

The patients will be carefully examined at baseline, re-examined after one week of treatment, and again after the last treatment (three weeks after first acupuncture). There will be a four-week follow-up after completion of the acupuncture treatment.

#### Baseline assessments

Baseline assessments will be conducted before randomization, including gender and age of patients, clinical syndrome (left or right hemiplegia), diseased location and size, NIHSS and Fugl-Meyer assessment (FMA) scores, cognitive impairment based on the Montreal cognitive assessment (MoCA), and swallowing disorder according to the standardized swallowing assessment.

#### Primary outcome measurement

The primary outcome measurement in the study is the change in NIHSS scores for neurological deficit evaluation. NIHSS is a standardized stroke severity scale used to describe neurological deficits in stroke patients and it strongly predicts the likelihood of a patient’s recovery after stroke. The NIHSS comprises tests of 11 items including the level of consciousness, best gaze, visual field, facial palsy, motor arm, motor leg, limb ataxia, sensory ability, best language, dysphagia, and neglect. Total scores range from 0 to 42, with scores above 25 indicating very severe neurological impairment, scores of 5 to 24 suggesting moderately severe to severe impairment, and scores below 5 indicating mild impairment
[19]. Assessments will be conducted at baseline and at one, three and four-weeks follow-up.

